## Abstract

**Background:**

End-stage renal disease (ESRD) is the last stage of chronic kidney disease, mainly caused by type 2 diabetes mellitus and characterized by an increased mortality risk related to cardiovascular disease. Low-dose aspirin (acetylsalicylic acid or ASA) seems to effectively prevent cardiovascular events in patients with ESRD. However, the number of interventional studies in this population remains limited and the mechanisms of aspirin-related bleeding remain poorly understood. Aspirin’s efficacy and safety may be modified by the presence of type 2 diabetes mellitus or platelet hyperreactivity.

**Objective:**

The overall objective of this protocol is to (1) evaluate aspirin’s safety and efficacy in reducing the risk of thrombotic events in patients with ESRD on hemodialysis and (2) examine whether aspirin’s efficacy is modified by the presence of type 2 diabetes mellitus or platelet hyperreactivity. Specifically, the primary objective is to compare the 12-month rate of any thrombotic event (cardiac death, nonfatal myocardial infarction, nonfatal stroke, arteriovenous fistula thrombosis) and Thrombolysis in Myocardial Infarction (TIMI) major bleeding in patients treated with aspirin compared to those on placebo. Secondary objectives are to test for effect modification of treatment by the presence of type 2 diabetes mellitus or platelet hyperreactivity and compare the rate of TIMI minor bleeding between treatment groups.

**Methods:**

We developed a protocol for a phase 2 randomized, single-center, placebo-controlled, triple-blind, superiority clinical trial to assess the prophylactic efficacy and safety of aspirin in patients with ESRD and on hemodialysis. It follows the ethical principles of the Declaration of Helsinki of the World Medical Association. A total of 342 participants would be enrolled over 12 months at a large dialysis center. Patients will be randomized in a 1:1 ratio and stratified by presence of type 2 diabetes mellitus and platelet hyperreactivity to receive either oral aspirin (100 mg/d) or placebo for a treatment period of 12 months. An intention-to-treat statistical analysis will be performed.

**Results:**

The randomized clinical trial will be performed after approval by the ethical committee of the participating center and registration at ClinicalTrials.gov.

**Conclusions:**

We provide a protocol for a randomized controlled trial to evaluate the safety and efficacy of treatment with aspirin to reduce the risk of thrombotic events. In addition, such a study would further our understanding of the mechanism of aspirin-related bleeding and help identify subgroups of best-responders and patients with a higher risk of adverse events.

**Registered Report Identifier:**

RR1-10.2196/10516

**Protocol**

## Introduction

### Background and Rationale

Chronic kidney disease (CKD) is a pathology defined by a decrease in glomerular filtration rate (GFR) below 60 mL/min/1.73 m^2^ or by the presence of kidney damage for at least 3 months [1]. It affects 200 million people worldwide, and the main risk factor for this disease is diabetes mellitus [2-4]. The life expectancy of CKD patients decreases with the severity of kidney impairment [5]. The most severe stage is end-stage renal disease (ESRD) and refers to patients undergoing renal replacement therapy (RRT) or for whom the GFR is lower than 15 mL/min/1.73 m^2^ [1]. The high risk of mortality observed in patients with ESRD is mainly due to cardiovascular events, the risks of which are 10- to 20-fold higher in these patients compared to non-CKD subjects and are significantly increased by the presence of diabetes mellitus [4,6,7]. In order to prevent cardiovascular events, patients with ESRD receive anticoagulant or antiplatelet therapy [8,9].

The benefits of low doses (75 to 100 mg/d) of aspirin (acetylsalicylic acid or ASA), an antiplatelet agent, as prophylactic drug for some specific types of cardiovascular events (atherosclerotic and ischemic events) in CKD and patients with ESRD have been reported in several studies. For instance, the impact of low-dose aspirin (75 mg/d) versus placebo on the risk of cardiovascular events was reported in an interventional study of 3619 CKD patients with hypertension (eGFR <60 mL/min/1.73 m^2^ at enrollment) [10]. The hazard ratio (HR) of cardiovascular events decreased by 15% (HR 0.85, 95% CI 0.61 to 1.17; *P*=.03) in patients with an eGFR of 45 to 59 mL/min/1.73 m^2^ and 66% for patients with eGFR <45 mL/min/1.73 m^2^ (HR 0.34, 95% CI 0.17 to 0.67; *P*<.05) [10]. Among secondary end points, a 36% reduction in the rate of myocardial infarction (HR 0.64, 95% CI 0.39 to 1.03; *P*=.08) was observed in patients with an eGFR of 45 to 59 mL/min/1.73 m^2^, and subjects with eGFR <45 mL/min/1.73 m^2^ had a rate reduction of 69% (HR 0.31, 95% CI 0.11 to 0.85; *P*<.05). Stroke, cardiovascular mortality, and total mortality were also reduced by 50% to 80% in patients with eGFR <45 mL/min/1.73 m^2^ receiving aspirin compared to placebo [10]. A systematic review of 2572 randomized controlled trials, meta-analyses, and systematic reviews (27 retained) reported that aspirin was associated with a 6% reduction in the relative risk (RR) for all-cause mortality (RR 0.94, 95% CI 0.88 to 1.00), 10% reduction in major cardiovascular events (RR 0.90, 95% CI 0.85 to 0.96), and 15% reduction in total coronary heart disease (RR 0.85, 95% CI 0.69 to 1.06) [11]. Last, a large case-control observational study performed on stroke patients with ESRD undergoing dialysis between 1998 and 2006 and exposed (n=763) or not (n=666) to aspirin (80 to 325 mg/d) showed significantly lower rates of all-cause mortality (HR 0.671, 95% CI 0.580 to 0.777; *P*<.001) and readmission to hospital for ischemic stroke (HR 0.715, 95% CI 0.580 to 0.882; *P*=.002) in the group receiving aspirin versus placebo, without any significant increase of risk of bleeding (*P*=.29) [12].

However, there is a lack of information about the prophylactic efficacy of aspirin for all types of thrombotic events that patients with ESRD may develop. There is also a gap of knowledge concerning the safety profile of aspirin in patients with ESRD. Concerning the risk of aspirin-related bleeding, there is some discrepancy between the results of observational and interventional studies, as an increased risk of bleeding has been reported in some observational studies [13,14]. However, interventional studies of patients with ESRD have found that low doses of aspirin are not associated with an increased risk of major bleeding in dialysis patients, despite an apparent increased risk of minor bleeding (eg, gastrointestinal bleeding) [10,15]. This discrepancy highlights the fact that the mechanism of aspirin-related bleeding events is not yet fully understood. Some authors have suggested that the prophylactic efficacy of aspirin and risk of bleeding related to this drug may be influenced by a phenomenon of platelet hyperreactivity [16]. However, further research is necessary to establish the real impact of platelet hyperreactivity on aspirin’s safety profile in patients with ESRD.

### Objectives

The primary and secondary objectives of this study are to evaluate aspirin’s prophylactic efficacy and safety in patients with ESRD. This will include (1) the assessment of aspirin prophylactic efficacy for all types of thrombotic events that patients with ESRD may develop, namely nonfatal stroke, nonfatal myocardial infarction, arteriovenous fistula thrombosis, and cardiac mortality, and (2) the assessment of aspirin-related major bleeding events using Thrombolysis in Myocardial Infarction (TIMI) criteria [17-19]. The study’s secondary objectives are to test for effect modification of treatment by the presence of type 2 diabetes mellitus or platelet hyperreactivity and compare the rate of TIMI minor bleeding between treatment groups.

Our hypothesis is that aspirin is superior to placebo as prophylactic therapy for thrombotic events in patients with ESRD on hemodialysis without increasing the risk of major bleeding.

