## Methods

### Participants, Interventions, and Outcomes

#### Study Design

We will perform a phase 2 randomized, single-center, placebo-controlled, triple-blind, superiority clinical trial with 1:1 allocation to receive either 100 mg of aspirin per day or placebo by mouth for 12 months. Randomization will be stratified based on 2 baseline characteristics: (1) the presence versus absence of type 2 diabetes mellitus and (2) the presence versus absence of platelet hyperreactivity. The study will start following approval of the Institutional Review Board (IRB) and will follow the ethical principles of the Declaration of Helsinki of the World Medical Association. The study design is illustrated in Figure 1.

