#### Sample Size

Sample size was calculated based on estimates for the rate of events in the primary composite outcome over 1 year: TIMI major bleeding (placebo 1% vs aspirin 2.5% [15]), cardiovascular events (placebo 3.0% vs aspirin 2.5% [10]), and fistula thrombosis (placebo 19% vs aspirin 8% [23]), for a total 1-year event rate of 23% in the placebo group and 13% in the aspirin group. A sample size of 318 patients (159 per arm) provides 80% power to detect a difference between groups of this magnitude (corresponding to an HR of 0.53) using a 2-sided log-rank test and alpha=.05 (Power Analysis and Sample Size Software version 14, NCSS LLC). The sample size for the trial was increased to 342 patients (171 per arm) to account for estimated attrition of 10%.

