#### Statistical Methods

Statistical analysis will be performed including all randomized patients according to their assigned treatment group (ie, intention-to-treat). The software used will be Stata 14 (StataCorp LLC). All testing will be 2-sided with statistical significance defined as *P*<.05. The primary composite outcome (first time-to-event of thrombotic events and TIMI major bleeding) will be analyzed with Kaplan-Meier curves and a log-rank test to detect difference between the groups. Cox proportional hazards regression may be used to adjust for relevant covariates, if appropriate (eg, for any unbalanced baseline characteristics that may occur by chance). Similarly, secondary outcomes will be analyzed with Kaplan-Meier curves and log-rank tests for all events. For the secondary objectives, interaction terms will be included in the Cox models above to test for interaction between treatment status and (1) the presence of type 2 diabetes and (2) platelet hyperreactivity. The proportion of patients with TIMI minor bleeding in each group will be compared with a chi-square test. If necessary, multiple imputation will be used for missing data.

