### Strengths and Limitations

The main strength of the trial is its study design, which includes allocation concealment, randomization, and triple-blinding in order to reduce possible bias. In addition, stratification will balance 2 variables that are strongly associated with the outcome, type 2 diabetes mellitus and platelet hyperreactivity, and will allow us to explore whether patients with these characteristics differentially respond to aspirin therapy. Overall, the study protocol is feasible for both investigators and patients, as study enrollment and subsequent visits will take place during or following the patients’ standard hemodialysis sessions.

Potential limitations of the study protocol include the difficulty in interpreting a composite outcome. The use of a composite primary outcome is supported by the fact that major bleeding rates are very rare, requiring a large sample size and lengthy study duration that would render the trial unfeasible. We address this issue by adding efficacy outcomes related to thrombosis to major bleeding outcomes. In order to clarify interpretation of the primary composite outcome, they are individualized in the secondary analysis. Regarding the study population, peritoneal dialysis patients will not be included as most do not have arteriovenous fistula and, hence, are not at risk for fistula thrombosis. Furthermore, glomerular disease patients who developed ESRD will not be included, as they show a different pattern of morbidity and mortality [20]. Another limitation is the possibility that we do not meet the planned recruitment time, as it will affect study power and validity. For that matter, we allow 12 more weeks for recruitment than initially planned. Last, despite the simplicity of drug administration, adherence is always a potential problem, which will be dealt with by identification of nonadherent patients and systematic training.

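### The hypothesis of no increase in major bleeding cannot be supported by a superiority trial that expects about 6 major bleeds and is sized on a rise from 1% to 2.5%

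*Protocol article*

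**What the plan says.** - **Objectives.** The hypothesis has an efficacy half and a safety half: "aspirin is superior to placebo as prophylactic therapy for thrombotic events in patients with ESRD on hemodialysis without increasing the risk of major bleeding".
- **Study Design.** The trial is a "triple-blind, superiority clinical trial with 1:1 allocation". No margin or bound is attached to the safety half.
- **Sample Size.** One of the three inputs to the composite event rate is "TIMI major bleeding (placebo 1% vs aspirin 2.5" per cent). The others are cardiovascular events (3.0% vs 2.5%) and fistula thrombosis (19% vs 8%). The totals are 23% and 13%, and the size is 318 (159 per arm), raised to 342 (171 per arm). No power is given for major bleeding alone.
- **Statistical Methods.** "All testing will be 2-sided with statistical significance defined as" P<.05. Major bleeding enters the primary outcome as one component of a first-event composite, and "secondary outcomes will be analyzed with Kaplan-Meier curves and log-rank tests for all events".
- **Strengths and Limitations.** Major bleeding is called too rare for a feasible trial of its own, which is the reason given for the composite. The components are then separated: "they are individualized in the secondary analysis".

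**The concern.** A two-sided superiority test can show that bleeding rises. It cannot show that bleeding does not rise; that takes an estimate precise enough to exclude a rise that matters. The protocol hypothesises no increase, names only superiority testing, and sizes the trial on rates in which bleeding is 2.5 times as frequent on aspirin. The hypothesis and the planning rates pull in opposite directions, and the expected number of bleeds is too small for the trial to tell them apart.

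At stake is false reassurance. The Discussion says the trial will provide safety data and may help revise international guidelines. A positive composite together with a non-significant bleeding comparison is the most likely outcome under the plan's own rates, and it would look like confirmation of both halves of the hypothesis.

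**Working it through.** **Inputs (Sample Size, Statistical Methods).** Major bleeding 1% vs 2.5% at 1 year; composite 23% vs 13%; 159 or 171 per arm; two-sided alpha 0.05; 12 months of follow-up for the outcome.

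**1. The plan's own figures.** The totals add up: 1 + 3 + 19 = 23 and 2.5 + 2.5 + 8 = 13. The hazard ratio reproduces: ln(0.87)/ln(0.77) = 0.533, against the stated 0.53. The stated 80% power at 318 does not reproduce with a fixed 12 months of follow-up per patient (64% to 67%, depending on method). It is roughly recovered (81%) only if patients accrue over 12 months and are followed to a common closing date. That is a separate matter, but step 4 checks the bleeding result under both readings.

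**2. Expected major bleeds.** n × (0.01 + 0.025):
- 159 per arm: 5.6
- 171 per arm: 6.0 (1.7 on placebo, 4.3 on aspirin)

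**3. Power of a test of bleeding alone, 1% vs 2.5%.** As a rough guide at 171 per arm, the pooled rate is 1.75% and the standard error of the difference is √(2 × 0.0175 × 0.9825/171) = 1.42 points. The expected z is 1.5/1.42 = 1.06, against a critical value of 1.96. More exactly:

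| Method | 159 per arm | 171 per arm |
|---|---|---|
| Chi-square, exact enumeration | 15.6% | 16.5% |
| Log-rank, 20,000 simulated trials | 15.0% | 16.9% |

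The assumed rise is missed 83% to 85% of the time. Power of 80% would need about 1,199 per arm by the two-proportion formula.

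**4. Sensitivity to follow-up.** With a common closing date there would be 8.3 to 8.9 bleeds and 24% to 25% power, so the rise is still missed about 75% of the time.

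**5. Can a favourable composite stand in?** The assumed contributions to the difference, aspirin minus placebo, are:
- fistula thrombosis: 8 − 19 = −11 points
- cardiovascular events: 2.5 − 3.0 = −0.5 points
- major bleeding: 2.5 − 1 = +1.5 points
- net: −10 points

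The composite favours aspirin while bleeding rises. In simulation at 171 per arm (thrombotic events 22% vs 10.5%, bleeding 1% vs 2.5%, independent exponential times, no dropout), the composite was significant for aspirin in about 69% of trials. It was significant with bleeding non-significant in about 60%. So about 87% of composite-positive trials would have a non-significant bleeding test although bleeding was truly 2.5 times as frequent.

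**6. Precision available.** At the assumed rates and 171 per arm, the 95% interval for the difference is 1.5 ± 1.96 × 1.42, or −1.3 to +4.3 points. For small counts, the Newcombe upper bound is d + √[(u_A − p_A)² + (p_P − l_P)²], with Wilson limits l and u in each arm (A aspirin, P placebo). The limits are 0.32% to 4.16% for 2/171 (1.17%) and 0.91% to 5.86% for 4/171 (2.34%):
- 2 placebo vs 2 aspirin: 0 + √(2.99² + 0.85²) = +3.1 points
- 2 placebo vs 4 aspirin: 1.17 + √(3.52² + 0.85²) = +4.8 points

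Neither excludes the +1.5-point rise in the Sample Size section, even when the observed counts are equal.

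**The case against.** **The decision rule is inferred.** A reader might conclude that the protocol will declare aspirin safe if P>.05. No section says so. Objectives also describes the safety aim as an assessment of major bleeding, which an estimate would satisfy. The log-rank test of bleeding alone comes from joining Statistical Methods with Strengths and Limitations; the formal list of secondary outcomes names TIMI minor bleeding and effect modification. This stands, so the point is limited to what the stated design can support.

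**The plan does not necessarily expect its hypothesis to fail.** That is another tempting inference. The 1% and 2.5% are planning inputs from a cited source that the Background also cites for no increased risk of major bleeding. Loading extra bleeding on aspirin makes the composite calculation more conservative and need not commit the authors to that increase. This stands too; what remains is a tension that the text should reconcile.

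**Non-significance is not guaranteed whatever the truth.** A fivefold rise (1% vs 5%) would be detected about 60% of the time by log-rank at 171 per arm. The weakness is specific to rises of the size that the plan assumes. Fisher's test would give a miss rate of about 93%, but the plan does not name it for bleeding, so that figure is not relied on.

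**The limitation is disclosed, and reporting detail belongs in the analysis plan.** Strengths and Limitations admits that bleeding is too rare to study alone, low power for a rare component is usual in phase 2, and an unseen analysis plan could specify confidence intervals. But the admission leaves the hypothesis unchanged, and its remedy of pooling does not inform the bleeding question (step 5). A later interval would not make the stated hypothesis supportable at this sample size.

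**Conclusion.** The point holds in this form: under the stated design, neither a non-significant comparison of major bleeding nor a favourable composite can support "without increasing the risk of major bleeding". About 6 major bleeds are expected, and the rise assumed in the Sample Size section would be missed about 83% to 85% of the time, or about 75% with follow-up to a common closing date. This rests on the plan's own rates, 159 to 171 per arm, and a two-sided log-rank or chi-square test of bleeding alone.

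The documents do not show that the authors will misread P>.05, and the absence of a non-inferiority margin is not the defect. With an upper bound of +3.1 points even at 2 vs 2 bleeds, a margin near the planned 1.5-point rise could not realistically be met. The defect is a hypothesis that conflicts with the planning rates and asks more of the trial than its size allows.

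**What to change.** - **Objectives:** restate the hypothesis as superiority of aspirin on thrombotic events, with its effect on major bleeding to be estimated. Reconcile this wording with the 1% and 2.5% in Sample Size, for example by saying whether those rates are a belief about aspirin or a conservative planning input.
- **Statistical Methods:** report major bleeding as a hazard ratio and a 12-month risk difference, each with a two-sided 95% confidence interval. State that P>.05 will not be read as no increase.
- **Sample Size or Statistical Methods:** state the expected precision. With 171 per arm, the upper bound for the risk difference is about +3.1 points at 2 vs 2 bleeds and +4.8 points at 2 vs 4, so at such counts the planned +1.5-point rise cannot be excluded.

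No non-inferiority margin is needed. The cost is a few sentences, with no extra patients, visits or data. The downside is that the sponsor gives up a safety claim this sample size cannot support.

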## Methods

### Participants, Interventions, and Outcomes

#### Study Design

We will perform a phase 2 randomized, single-center, placebo-controlled, triple-blind, superiority clinical trial with 1:1 allocation to receive either 100 mg of aspirin per day or placebo by mouth for 12 months. Randomization will be stratified based on 2 baseline characteristics: (1) the presence versus absence of type 2 diabetes mellitus and (2) the presence versus absence of platelet hyperreactivity. The study will start following approval of the Institutional Review Board (IRB) and will follow the ethical principles of the Declaration of Helsinki of the World Medical Association. The study design is illustrated in Figure 1.

#### Study Setting

The trial involves patients on chronic intermittent hemodialysis and will be conducted in a large dialysis center (ie, with ≥2000 patients on RRT).

#### Eligibility Criteria

The study population consists of men or women with ESRD who are at least 18 years of age and have started chronic intermittent hemodialysis in the previous 3 months.

Exclusion criteria include any contraindications to ASA, concurrent treatment with anticoagulants or platelet aggregation inhibitors, and pregnancy or lactation. Patients with life-threatening conditions other than renal or vascular disease will also be excluded from the trial: all types of cancer, liver disease, AIDS, or severe lung disease. ESRD due to glomerulopathy has a different pattern of mortality [20], which precludes its inclusion in this trial. Patients on other modalities of RRT will also be excluded.

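### The planned 23% vs 13% treats every patient as at risk of fistula thrombosis, but eligibility sets no vascular-access criterion; any patients without a fistula would cost power

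*Protocol article*

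**What the plan says.** **Eligibility Criteria.** Participants are adults with ESRD who "have started chronic intermittent hemodialysis in the previous 3 months". The exclusions cover contraindications, concurrent antithrombotic drugs, pregnancy or lactation, other life-threatening disease and ESRD from glomerulopathy. On dialysis itself the only exclusion is by modality: "Patients on other modalities of RRT will also be excluded". Vascular access is mentioned in neither list.

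**Sample Size.** Three one-year component rates are added: major bleeding 1% placebo and 2.5% aspirin, cardiovascular events 3.0% and 2.5%, fistula thrombosis 19% and 8%. They are summed "for a total 1-year event rate of 23% in the placebo group and 13% in the aspirin group", given as an HR of 0.53. The section concludes: "A sample size of 318 patients (159 per arm) provides 80% power" for a 2-sided log-rank test at alpha 0.05.

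**Strengths and Limitations.** The choice of population is explained partly by fistula status: "peritoneal dialysis patients will not be included as most do not have arteriovenous fistula and, hence, are not at risk for fistula thrombosis".

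**Study Design and Statistical Methods.** Randomization is stratified by type 2 diabetes and platelet hyperreactivity, not by access. All randomized patients are analyzed in their assigned group.

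**The concern.** The protocol accepts that a patient without a fistula is not at risk of fistula thrombosis, and uses this to leave out one dialysis modality. It does not carry the reasoning over to hemodialysis patients who lack a fistula. They may enroll, and they stay in the denominator of the intention-to-treat analysis. The sample size nevertheless gives the fistula component full weight, which amounts to assuming that every patient carries the risk behind the 19% and 8%.

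This component supplies the whole planned benefit. It contributes 11 points in favor of aspirin (19 − 8). The other components together are 4% on placebo and 5% on aspirin, 1 point against aspirin, which leaves the planned 10. On the protocol's own figures, patients without a fistula would therefore contribute few events and no net benefit. At stake are the assumed event rate, the assumed HR and hence the power.

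**Working it through.** **Inputs from the Sample Size section.** Component rates as above; N = 318; 2-sided alpha 0.05; target power 80%. The outcome window is 12 months (Outcomes section).

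**Inputs not in the documents, so assumed.** (a) The 19% and 8% are rates among patients with a fistula. (b) A share f of enrolled patients has one, constant over 12 months. Values 0.9, 0.8 and 0.5 are shown as a range, not as estimates.

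**Step 1: the plan's own figures (f = 1).**
- Placebo 1 + 3 + 19 = 23%; aspirin 2.5 + 2.5 + 8 = 13%. Reproduced.
- HR = ln(1 − 0.13)/ln(1 − 0.23) = 0.533. Reproduced as 0.53.
- Schoenfeld events for 80% power = 4(1.960 + 0.842)²/(ln 0.533)² = 79.2, so 80. With 12 months of follow-up the mean event probability is (0.23 + 0.13)/2 = 0.18, so N = 80/0.18 = 444.4, or 445. The stated 318 is not reproduced; at 318 the power is 0.663.
- One variant comes near 318: uniform accrual over 12 months with everyone followed to month 24. The mean event probability is then 0.2551, N = 314, and power at 318 is 0.809. This does not match the 12-month outcome window.

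The gap between 80% and 0.663 exists with no dilution at all. The losses below are therefore measured from each f = 1 baseline, not from 80%.

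**Step 2: dilution.** Placebo = 4% + 19%·f; aspirin = 5% + 8%·f; difference = 11f − 1 points. HR = ln(1 − aspirin)/ln(1 − placebo). Events = 318 × mean event probability. Power = Φ(√events × |ln HR|/2 − 1.960).

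Example, f = 0.8: placebo 4 + 15.2 = 19.2%; aspirin 5 + 6.4 = 11.4%; HR 0.568; events 318 × 0.153 = 48.7; power = Φ(1.974 − 1.960) = 0.506.

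| f | Placebo vs aspirin | HR | Power at 318, 12 months (loss in points) | Power at 318, 12+12-month variant (loss in points) | N for 80%: 12 months / variant |
|---|---|---|---|---|---|
| 1.0 | 23.0% vs 13.0% | 0.53 | 0.663 | 0.809 | 445 / 314 |
| 0.9 | 21.1% vs 12.2% | 0.55 | 0.588 (7.5) | 0.740 (6.9) | 529 / 372 |
| 0.8 | 19.2% vs 11.4% | 0.57 | 0.506 (15.7) | 0.656 (15.3) | 641 / 448 |
| 0.5 | 13.5% vs 9.0% | 0.65 | 0.250 (41.3) | 0.341 (46.8) | 1512 / 1042 |

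Simulation with 10,000 runs at 12 months gave 0.64, 0.49 and 0.25 for f = 1, 0.8 and 0.5, in line with the formula.

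**The case against.** The best reply is that the dilution is conditional. The documents give no fistula share, and the study cited for the 19% and 8% is not at hand. If those rates already come from a population with mixed access, they need no discount. If f is close to 1, the effect is small. This stands, and it is why the result is a range.

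Second, access may change. Patients enter within 3 months of starting hemodialysis and are followed for 12 months. Anyone who receives a fistula in that time becomes at risk, so a baseline share would overstate the loss. This also stands, although such patients are at risk for only part of the year.

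Third, a reader might infer that the protocol contradicts itself. It does not quite do so. The Discussion says that most peritoneal dialysis patients lack a fistula and uses this to exclude a modality; it does not promise that every participant has one. The objectives address patients with ESRD on hemodialysis and cover several thrombotic events, so a broad population may be deliberate. That is a legitimate choice, but the event rates should then match it.

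Fourth, the article condenses a fuller protocol. However, it sets out its eligibility criteria in detail and explains the population by fistula status, and the sample size shows the fistula rates entering undiscounted. If a fuller document contains an access criterion, the remedy is simply to state it.

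**Conclusion.** The point holds in conditional form. The planned 23% vs 13% rests on an unstated assumption that all enrolled patients carry the fistula thrombosis risk behind the 19% and 8%, and the eligibility criteria do not secure it. If those are rates per patient with a fistula and access is fixed over the year, dilution alone costs about 7 points of power at f = 0.9, 15 to 16 at f = 0.8 and 41 to 47 at f = 0.5. The loss at 0.9 and 0.8 is nearly the same under both follow-up assumptions.

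Three stronger readings are tempting and are not supported:
- That the trial will be diluted by a known amount. Neither f nor the denominator of the cited rates is given.
- That access type explains a fall from 80% to 51% or 25%. The drop from 80% to about 66% at 12 months is a separate sample-size problem, present with f = 1.
- That the comparison is biased. Access is a pre-randomization characteristic; leaving it open affects power and interpretation, not the validity of the randomized comparison.

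**What to change.** Record vascular access (fistula or other) at baseline. Prespecify it as a stratum in the log-rank test or a covariate in the Cox model. In the Sample Size section, state the population to which the 19% and 8% refer. If they are per patient with a fistula, weight them by the expected share at risk, allowing for fistulas created during follow-up, and restate the event rates, HR and power. Check the source first: weighting rates that already come from a mixed-access population would discount them twice.

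The cost is one baseline field, one line of analysis text and a recalculation. The stratum or covariate does not restore lost events, so holding 80% power may need more patients (last column of the table). The Results section says the trial is not yet submitted or registered, so the change can be made before it starts. The center's share can be filled in once a center is chosen.

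Alternatively, require a fistula at randomization, on the ground already used for peritoneal dialysis. This is one inclusion line. It slows recruitment and narrows the question to hemodialysis patients with a fistula, so the objectives would have to say so.
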